**5.3. Indicate the total duration of a participant's involvement.**

15-minute online purchasing task and survey

**5.4. Indicate the total number of participants to be screened (if applicable) and/or enrolled (i.e., signed consent form). If the proposed research involves secondary data analyses only, indicate the number of data, documents, records, and/or specimens that will be obtained.**

5,000 participants will be recruited to take part in our study.

**5.5. List inclusion and exclusion criteria, including age ranges of all participants, and describe the screening process. Provide a rationale for any specific exclusion criteria.**

We will recruit 5,000 primary caregivers of children 0-5 years old to participate in a randomized controlled online shopping experiment, with oversampling for Hispanic and black participants. We will use Qualtrics, a firm that recruits research participants through their online panels and other online communities, social networks, and websites, to recruit participants with the following eligibility criteria: 1) primary caregiver of a child 0-5 years old; 2)  $\geq 18$  years old; and 3) U.S. citizen. For our study, participants will be sent an invitation asking them to "take a survey" to avoid selection bias based on survey topic. Participants will also be required to answer a data integrity check question near the end of the survey (i.e., "what month is it?"). Those who answer incorrectly will be excluded from analyses.

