**Label Randomization.** Caregivers will be randomized using simple randomization via the Qualtrics platform to see fruit drinks in our online store and survey with one of the following seven label conditions (**Appendix B**). The first condition (*claim & imagery*, control) will represent the status quo and contain a 100% Vitamin C claim and fruit imagery. Conditions 2-4 will involve the removal of package elements for fruit drinks high in added sugar (“high sugar”,  $\geq 10\text{g/serving}$ , 20% DV): Condition 2 (*imagery only*) will have fruit imagery but no 100% Vitamin C claim on high-sugar fruit drinks; Condition 3 (*claim only*) will have a 100% Vitamin C claim but no fruit imagery on high-sugar fruit drinks; and Condition 4 (*no claim or imagery*) will feature no imagery or claims on high-sugar fruit drinks. Conditions 5-7 will involve the addition of package elements. Condition 5 (*imagery, claim, & text % fruit juice disclosure*) will show a text description of the percent fruit juice in each fruit drink, to see if it changes the effects of the claim and imagery. The sixth (*imagery, claim, & added sugar warning*) and seventh conditions (*imagery, claim, & added sugar warning w/teaspoons of sugar*) will test the effects of added sugar warnings.

**Primary Outcomes:** The primary outcomes will be total calories and grams of added sugar purchased in the online store task (averaged by condition). We will also examine the percentage of people in each condition that purchased a drink high in added sugars ( $>20\%$  DV) for their child, and the percentages that chose each category of drink (fruit drinks, 100% juice, etc).

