**16. Data/Statistical Analyses Plan**

**16.1. Describe plans for analysis (including the statistical method, if applicable).**

Linear regression will be used to examine mean total calories and grams of added sugar purchased between our experimental groups. Logistic regression will be used to compare proportions in each condition that chose different beverage types. Because of the randomized design, the only covariates we will control for will be purchasing frequency (for secondary outcomes), and those that may by chance significantly differ among the groups. A Bonferroni-Holm correction will be used to control for multiple comparisons. In secondary analyses we will stratify the main effects by SNAP/WIC status, race/ethnicity, household income, and frequency of child fruit drink consumption.

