**16.2. Is there a sample size/power calculation?**

☐ No ☒ Yes: *If yes, describe the calculation and the scientific rationale, and, if applicable, by site and key characteristics such as participant demographics.*

To compare the primary outcome of total kcals purchased across the seven groups, we determined that a sample of 4,900 participants (700 per group) would provide at least 80% power to detect an 18-kcal difference between each group, assuming an alpha of 0.05. This estimate is based on effect sizes found in our previous labeling research. It is typical to exclude a small number of participants in online studies (e.g., for failing data integrity check questions), so we will recruit 5,000 participants. Qualtrics has confirmed that this will be feasible given our inclusion criteria.

**17. Costs and Compensation** ☐ N/A. *Skip to next section.*

**17.1. Identify any costs that participants may incur during the study, including transportation costs, childcare, or other out-of-pocket expenses.**

None

**17.2. Identify remuneration that participants may receive during the study. Specify the amount, timing of disbursement, and method (e.g. money, gift cards, in-kind, incentives, raffles, and transportation). Describe how compensation will be calculated and paid if a participant withdraws. If any participant will receive a single payment more than \$100, or \$600 or more in one calendar year, refer to [Harvard University Financial Policy on Human Subject Payments](#).**

Participants will receive a \$5 gift card at the end of their participation in the study, dispensed through Qualtrics via participant emails. They will receive compensation regardless of whether they stop the study early.

**18. Sharing Study Results** ☐ N/A. *Skip to next section.*

**18.1. Describe the plan to share study results with individual participants, the participant group/community, and/or others.**

Results will be published in a scientific journal, and will be shared via webinar with the FDA.

**19. Research Related Injuries** ☒ N/A. *Skip to next section.*

19.1. Describe plans for medical care and compensation for research-related injuries.

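### Section 16.1 chooses covariates for the primary models by baseline significance tests, so the primary model is not fixed in advance and the rule recovers almost none of the precision that fixed adjustment could give

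*Protocol*

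**What the plan says.** Section 5.6 defines the endpoints: "The primary outcomes will be total calories and grams of added sugar purchased in the online store task". Section 16.1 sets the model: "Linear regression will be used to examine mean total calories and grams of added sugar purchased between our experimental groups". On adjustment, section 16.1 says that "the only covariates we will control for will be purchasing frequency (for secondary outcomes"), "and those that may by chance significantly differ among the groups".

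The word "only" makes this an exclusive rule. Purchasing frequency is limited to secondary outcomes, so no covariate is fixed for the primary outcomes. Whatever enters those models enters because a baseline test was significant. Nothing elsewhere in the protocol replaces the rule.

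Three other statements bear on the point:

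- Allocation, section 5.6: "Caregivers will be randomized using simple randomization via the Qualtrics platform".
- Secondary analyses, section 16.1: "we will stratify the main effects by SNAP/WIC status, race/ethnicity, household income, and frequency of child fruit drink consumption".
- Recruitment, section 5.5: "with oversampling for Hispanic and black participants".

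**The concern.** With simple randomization, every baseline difference between arms is due to chance, as the rule itself acknowledges. Adjustment is useful when a covariate predicts the outcome, and a balance p-value carries no information about that. The rule can admit a variable unrelated to beverage choice because it happened to reach significance, and leave out a strongly predictive one because it did not.

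Two things are at stake. First, the primary model depends on the data it is meant to analyse, and because the candidates and the threshold are open, the analyst has room to choose. That matters for a trial whose results are meant to inform federal label regulation. Second, whatever precision the survey's own baseline variables could add is mostly lost. The rationale offered, that the design is randomized, supports either no adjustment or adjustment fixed in advance. It does not support adjustment triggered by a test.

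**Working it through.** **Inputs.** From section 16.2: "a sample of 4,900 participants (700 per group) would provide at least 80% power" for an 18-kcal difference at alpha 0.05, seven groups. Two-sided testing is assumed. Three inputs are not in the protocol: the SD of calories purchased, the number of baseline candidates, and the share of outcome variance (R²) that covariates explain.

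**1. The plan's own figure.** No SD is stated, so 700 per group cannot be checked independently. It can only be inverted:

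SD = 18 / [(1.960 + 0.842) × √(2/700)] = 18 / 0.1498 ≈ 120.2 kcal.

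This SD returns 700 per group and 80% power by construction. It serves below only as a baseline.

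**2. How often the model changes by chance.** For k independent candidates tested at 0.05, the chance that at least one is selected is 1 − 0.95^k:

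| k | Chance |
|---|---|
| 5 | 22.6% |
| 8 | 33.7% |
| 10 | 40.1% |
| 12 | 46.0% |

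**3. What fixed adjustment could give.** The standard error is multiplied by √(1 − R²). The equivalent number of extra participants is 4,900 × [1/(1 − R²) − 1]. Power is Φ[2.802/√(1 − R²) − 1.960].

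| R² (assumed) | SE reduction | Equivalent participants | Power, 18 kcal |
|---|---|---|---|
| 0 | – | – | 80.0% |
| 0.05 | 2.5% | 258 | 82.0% |
| 0.10 | 5.1% | 544 | 84.0% |
| 0.15 | 7.8% | 865 | 86.0% |

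At R² = 0.02 the gain is negligible: 80.8%.

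**4. What the protocol's rule gives.** Simulation used 3,000 runs per setting, 4,900 participants, simple randomization to seven arms, 10 independent covariates, one arm compared with control, and selection by a baseline F-test at p < 0.05.

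| R² | Power: unadjusted | Power: protocol's rule | Power: fixed set | Type I error: protocol's rule |
|---|---|---|---|---|
| 0.10 | 80.7% | 80.9% | 84.0% | 4.4% |
| 0.30 | 79.5% | 80.3% | 91.1% | 4.9% |

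Simulation error on the type I figures is about 0.4 percentage points: √(0.05 × 0.95/3,000) = 0.004. The rule behaves much like no adjustment, because a given covariate is selected only about 1 time in 20.

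**The case against.** The strongest reply is that the rule is suboptimal but still valid, and much of this stands.

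- **Error rate.** A reader might infer that ignoring the selection step makes the confidence intervals and Holm-adjusted p-values too optimistic. The simulation does not support that: type I error was 4.4–4.9%. This holds for mechanical application and does not cover candidates chosen after looking at the data.
- **Effect on the estimate.** With the back-solved SD, one triggered covariate moves an arm-versus-control estimate by about 0.8 kcal on average if it explains 1% of variance, 1.9 kcal at 5% and 3.3 kcal at 15%. All are small against 18 kcal.
- **Selection probability.** The 23–46% assumes independence. With pairwise correlation of 0.5 (also an assumption) it falls to roughly 19% to one third. It is the chance that the model changes and should not be read as the chance of a wrong conclusion.
- **Prognostic value.** A reader might infer that known predictors are being discarded. The protocol gives no R² for any variable. It shows only that the investigators thought some variables relevant enough to stratify by, or to adjust for in secondary outcomes.
- **Race/ethnicity.** A reader might also infer that oversampling obliges the primary model to include it. Oversampling governs who is recruited. Allocation is not stratified, so no such obligation follows.
- **Scope.** A candidate list and test threshold may properly be left to an SAP that is not shown. The trigger itself is stated in the protocol and is open to criticism as it stands.

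None of this gives a reason to choose covariates by a balance test. Even a sponsor who prefers unadjusted primary models would need to delete the clause.

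**Conclusion.** The point holds as a weakness of a stated rule and should be corrected. The primary linear models have no fixed covariates, and significance in chance imbalances decides what enters. The 23–46% chance that at least one covariate enters rests on an assumed 5 to 12 independent candidates at 0.05. The rule recovers almost none of the precision that fixed adjustment could give. How much that is worth is illustrative: about 2 to 6 percentage points of power for 18 kcal if R² is 0.05–0.15, using an SD inferred from the plan's own sample size and the uncorrected alpha of section 16.2. The protocol supports no firmer figure. The case for change rests mainly on having a primary model that is known before the data are seen.

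**What to change.** In section 16.1, delete the significance trigger and state that no baseline significance tests will be used to choose covariates.

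For the primary linear models, pre-specify a short covariate set used regardless of balance, and report the unadjusted model as a sensitivity analysis. Draw the set from variables the survey already collects, for example child age, race/ethnicity, household income and SNAP/WIC status. Each must be measured before label exposure or be incapable of being affected by it. This needs confirming against the question order, because section 5.6 places the shopping task first and the questionnaire is in an appendix not available here.

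Keep purchasing frequency as the pre-specified covariate for secondary outcomes, subject to the same condition; a self-reported frequency asked after the labels may not meet it. For the logistic models, note that adjusted odds ratios are conditional, so the precision argument above does not carry over directly.

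The cost is a few degrees of freedom out of about 4,900 and a wording change. No new data are needed.

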**5.6. Describe study procedures.**

After providing informed consent, participants will complete a 10-15 minute survey. They will be asked to answer all questions based on their oldest child 0-5 years old, and will provide the age of the child. First, participants will be told to use a mock online retail store to choose a beverage for their child that will be sent to them (or they will receive \$5). In reality, at the end of the study, we will debrief participants on the study purpose and inform them that instead of receiving the beverage they selected, all participants will be compensated with \$5 through the survey distribution company (twice the value of a typical beverage in the store). This very minor deception enables us to incentivize participants to behave as they normally would when shopping online and to minimize potential social desirability bias introduced by participating in a study. Participants will then be shown images of 12 different beverages (random order) consisting of commonly purchased beverages in various categories, with oversampling for fruit drinks (e.g., 6 fruit drinks, 1 milk, 2 100% juices, 2 regular sodas, and 1 water). The variety will provide a realistic shopping scenario for generalizability. Participants will be required

to click on beverages to see an enlarged package before choosing. After selecting their beverage, participants will advance in the survey to view four randomly ordered fruit drinks one at a time and answer questions about their health knowledge, product beliefs, and purchase intentions. See **Appendix A** for full survey (consent + debriefing language) and **Appendix B** for images.

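### Bonferroni-Holm is valid here but mildly conservative: a step-down max-T test on the same family gains about 2-4 points of power per true effect within one outcome, and about 2-8 if both primary outcomes are adjusted jointly

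*Protocol*

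**What the plan says.** Section 5.6 randomizes caregivers to "one of the following seven label conditions". Condition 1 is the control, which "will represent the status quo and contain a 100% Vitamin C claim and fruit imagery". Each caregiver is told to "use a mock online retail store to choose a beverage for their child", and "The primary outcomes will be total calories and grams of added sugar purchased in the online store task". Section 16.1 analyses them in one way: "Linear regression will be used to examine mean total calories and grams of added sugar purchased between our experimental groups". Logistic regression follows for the drink-type proportions. After both models comes the only statement on multiplicity: "A Bonferroni-Holm correction will be used to control for multiple comparisons". The protocol does not say which contrasts form the family, or whether the two primary outcomes are adjusted together or separately. Section 16.2 says that 700 per group "would provide at least 80% power to detect an 18-kcal difference between each group", at alpha 0.05. It gives no standard deviation and mentions no adjustment.

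**The concern.** Holm compares ordered p-values with thresholds that must hold under the worst possible dependence between tests. In this trial the dependence is not unknown. With equal arms, two contrasts that share an arm have correlation 0.5 in absolute value, whatever the data turn out to be. Calories and added sugar are two attributes of the same chosen item, so their test statistics are correlated too. The planned linear regressions supply the estimated joint covariance of the contrasts.

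A procedure that ignores this runs below its nominal 5% family-wise error. At the margin it fails to declare label effects that an equally strict procedure would declare from the same data. What is at stake is a few points of power per true effect, not the validity of any claim.

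**Working it through.** **Inputs.** Seven arms with one control, and two primary outcomes from one drink (section 5.6); 700 per arm, 18 kcal, 80% power, alpha 0.05 (section 16.2). Assumed: two-sided tests, equal arms, and a between-outcome correlation ρ varied over 0.3-0.95. Milk and 100% juice carry calories without added sugar, which keeps ρ below 1.

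**The plan's own figure.** Without a stated SD it cannot be reproduced independently. Solving for the SD with no adjustment:

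SD = 18 / [(1.960 + 0.842) × √(2/700)] = 120.2 kcal.

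This returns 80.0% by construction and is used below as an assumption. The noncentrality of one contrast is then 2.802. Unadjusted power would be 92.0% at SD 100 and 67.2% at SD 140.

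**Correlation from shared arms.** For two contrasts with control, the covariance is σ²/n and each variance is 2σ²/n, so the correlation is 0.5.

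**First-step critical values.** Holm uses z at 1 − 0.05/(2m). Max-T uses the simulated 95th percentile of the largest |T|. Power for one contrast is Φ(2.802 − c); for example, Φ(2.802 − 2.638) = Φ(0.164) = 0.565. The n per arm for 80% power is 2[120.2(c + 0.842)/18]².

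| Family | c: Holm / max-T | Power: Holm / max-T | n per arm: Holm / max-T |
|---|---|---|---|
| 6 vs control, one outcome | 2.638 / 2.563 | 0.565 / 0.594 | 1,080 / 1,034 |
| 6 × 2 outcomes, ρ 0.5 | 2.865 / 2.794 | 0.475 / 0.503 | 1,226 / 1,179 |
| 6 × 2 outcomes, ρ 0.9 | 2.865 / 2.707 | 0.475 / 0.538 | 1,226 / 1,124 |
| 21 pairs, one outcome | 3.038 / 2.948 | 0.407 / 0.442 | 1,343 / 1,281 |
| 21 × 2 outcomes, ρ 0.9 | 3.241 / 3.090 | 0.330 / 0.386 | 1,487 / 1,379 |

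**Full step-down procedures, average power per true effect, Holm to max-T.**

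- Six contrasts, one outcome: 0.558 to 0.583 (one effective label), 0.585 to 0.608 (three), 0.670 to 0.685 (all six).
- 21 pairs, one outcome: 0.417 to 0.452 (one effective label), 0.447 to 0.477 (three).
- Six contrasts × two outcomes, one effective label: 0.489 to 0.537 at ρ 0.8, 0.484 to 0.544 at ρ 0.9, 0.490 to 0.565 at ρ 0.95.
- 21 pairs × two outcomes, ρ 0.9: 0.342 to 0.404 (one effective label), 0.354 to 0.423 (three). The pairwise runs used only 600 trials, so their levels are approximate.
- A separate run with two effective labels and ρ 0.3-0.9: 49-50% to 51-57% for 12 tests, and 35% to 38-41% for 42 tests.

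**Error rates.** Holm's family-wise error under the global null is 0.041 (6 tests), 0.032 (12 tests, ρ 0.9), 0.038 (21) and 0.032 (42, ρ 0.9). In the control-contrast families, max-T gave 0.049 and 0.052 under the global null. The Monte Carlo standard error is √(0.05 × 0.95/20,000) ≈ 0.0015, so both agree with 0.05. With one, three or five effective labels, max-T stayed at or below 0.045. In these control-contrast runs Holm never rejected a hypothesis that max-T retained.

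**The case against.** The strongest reply is that nothing in section 16.1 is wrong. Holm is a standard procedure with strong control, it needs no joint model, and choosing between valid procedures can be left to the SAP. A reader might infer from the conservatism that the planned analysis is faulty; the documents do not support that. What remains is that the protocol does name the method, and a uniformly no-worse alternative exists at little cost.

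Three further objections stand and limit the point.

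- **The family is not stated.** A reader might take the larger, joint-family gain as assured. It applies only if Holm spans both outcomes. If the team means Holm within each outcome, moving to a joint max-T would lose power: about 0.51-0.53 against 0.56-0.57 for six contrasts, and 37-41% against 43-44% for 21 pairs. Per-outcome Holm does not control error across both outcomes, but the protocol does not say that it must.
- **The Holm sentence also covers the logistic comparisons.** Replacing it outright with text on the primary outcomes would remove the correction for drink categories.
- **Permuting condition labels is not a safe route to max-T here.** Permuting all seven arms imposes the global null and does not guarantee strong control for pairwise contrasts when other arms differ. Section 16.1 also allows covariate adjustment for chance imbalances, which complicates simple permutation.

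**Conclusion.** The point holds as an optional efficiency improvement. For the same family and alpha, step-down max-T gains about 2-4 points of power per true effect when each outcome is adjusted separately. The gain shrinks to 1.5 points if all six labels work. In a joint two-outcome family it is about 2-8 points, with the upper end needing ρ near 0.95. These sizes rest on the implied SD of 120.2 kcal, two-sided tests, equal arms and large-sample normality, which is reasonable at 700 per arm.

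A reader might also infer that the change rescues the planned power. It does not. If the stated 80% is unadjusted, power for a single effective contrast in these families is about 0.34-0.56 with Holm and about 0.40-0.58 with max-T. If the 80% already allowed for adjustment, the SD would have to be smaller: about 97 kcal for 6 tests or 87 kcal for 21.

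**What to change.** Keep the Holm sentence in section 16.1 for the logistic (drink-category) comparisons. For the linear-regression comparisons of calories and added sugar, add:

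> Within the same family of comparisons to which Holm would have been applied, family-wise error will be controlled at 5% by a step-down max-T procedure using the estimated (robust) joint covariance of the regression contrasts, with a fixed seed.

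Do not widen the family to both outcomes as part of this change, and do not permute all seven labels for pairwise contrasts. If each outcome is its own family, the covariance from that outcome's regression is enough. If the family is joint, the cross-outcome covariance must be estimated as well.

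The cost is one sentence and a little code, settled before the data are analysed, with no extra participants. The downside is that adjusted p-values come from simulation and rely on joint normality, where Holm needs neither.

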### 1. Specific Aims

Test the independent and combined effects of common front-of-package (FOP) marketing tactics (e.g., 100% Vitamin C claims and fruit images) and added sugar warning labels and nutrition disclosures (e.g., teaspoons of added sugar per serving) on parents' perceptions and beverage choices for their children using a randomized controlled design in a unique online retail setting, and examine differences by race/ethnicity, income, and SNAP/WIC participation.

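### The aim asks whether label effects differ between subgroups, but the only subgroup method stated, stratification, neither estimates nor tests a difference

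*Protocol*

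**What the plan says.** Protocol section 1 (Specific Aims) states one aim: to test the label effects on parents' perceptions and beverage choices, "and examine differences by race/ethnicity, income, and SNAP/WIC participation".

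Protocol section 16.1 gives the analysis. For the main comparison, "Linear regression will be used to examine mean total calories and grams of added sugar purchased between our experimental groups", with logistic regression for the choice of beverage type. For subgroups the only sentence is "In secondary analyses we will stratify the main effects by SNAP/WIC status, race/ethnicity, household income, and frequency of child fruit drink consumption". On multiplicity, "A Bonferroni-Holm correction will be used to control for multiple comparisons"; the section does not say which comparisons form the family or whether the stratified results belong to it. No interaction term, heterogeneity test or rule for comparing strata appears anywhere in the protocol.

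Section 16.2 sizes the trial for overall pairwise comparisons only: 4,900 participants, 700 per group, which "would provide at least 80% power to detect an 18-kcal difference between each group, assuming an alpha of 0.05". No standard deviation is given.

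**The concern.** A question about differences in effect needs an analysis whose output is a difference in effect. A stratified analysis returns one label effect per stratum and leaves the comparison to the reader. The usual informal comparison is to note which strata reach significance. That is not a test of effect modification, because the verdict in each stratum depends on its size as well as on the effect in it.

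The use of the results makes this matter. Sections 2.2 and 13.1 say they are meant to inform federal rules on package labelling, section 18.1 plans to share them with the FDA, and section 5.5 oversamples Hispanic and black participants, so subgroup results will attract attention. A statement that a warning label works for one racial or income group and not another should rest on an estimate of that difference.

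**Working it through.** **Inputs**
- 700 per group, an 18-kcal difference, 80% power, alpha 0.05: section 16.2. Two-sided testing is assumed.
- Seven conditions, hence six contrasts with control: section 5.6.
- SD of kcal purchased: not stated. The protocol says only "This estimate is based on effect sizes found in our previous labeling research".
- Stratum sizes: not stated. Splits of 50/50, 30/70 and 20/80 are assumed.

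**Step 1. The plan's own figure.** Without an SD, the 700 per group cannot be reproduced independently; it can only be solved backwards. SD = 18 / [(1.960 + 0.842) × √(2/700)] = 120.2 kcal, which returns 700 per group and 80% power by construction. If the plan meant one-sided 0.05 the SD would be about 135; if it meant alpha 0.05/6, about 97.

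**Step 2. Power within a stratum, same 18-kcal effect in each.** Power = Φ(18 / [120.2 × √(2/n)] − 1.96), with n per arm in the stratum.
- 50/50 (n = 350): expected z = 2.80/√2 = 1.98, power 0.508. This needs no SD once 80% power at two-sided 0.05 is accepted.
- 30/70 (n = 210 and 490): 0.335 and 0.650.
- 20/80 (n = 140 and 560): 0.240 and 0.707.

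**Step 3. Chance of discordant verdicts.** The strata are independent, so the chance that one contrast is significant in exactly one of them is p₁(1 − p₂) + p₂(1 − p₁).

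| Split | alpha 0.05 | alpha 0.05/6 |
|---|---|---|
| 50/50 | 2 × 0.508 × 0.492 = 50% | 38% |
| 30/70 | 55% | 41.5% |
| 20/80 | 61% | 46% |

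At an SD of 97 to 100 and alpha 0.05, the range over these splits is 43% to 62%. With three or four equal strata, where per-stratum power is 0.366 or 0.288, mixed verdicts occur in 70% or 74% of trials. If all six labels had an 18-kcal effect, a simulation with a shared control gave at least one discordant contrast in about 95% of trials (50/50), and about three of six on average.

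**Step 4. Dependence on the true effect (50/50, SD 120, alpha 0.05).**
- Effect 0: 2 × 0.05 × 0.95 = 9.5%.
- Effect 18 kcal: 50%.
- Effect 36 kcal: power 0.977 per stratum, 2 × 0.977 × 0.023 = about 4%.

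**Step 5. What an interaction test can detect.** SE = SD × √(2/n₁ + 2/n₂); detectable difference at 80% power = (1.960 + 0.842) × SE for one unadjusted contrast.
- 50/50: SE = 120.2 × √(4/350) = 12.85, detectable difference 36.0 kcal.
- 30/70: 39.3 kcal.
- 20/80: 45.0 kcal.
- 50/50 at alpha 0.05/6: (2.638 + 0.842) × 12.85 = about 45 kcal.

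Power for an 18-kcal difference in effect is 29%, 25% and 20% for the three splits, unadjusted. Over the back-solved SD range of 97 to 135, the unadjusted 50/50 figure runs from 2.80 × 96.8 × √(4/350) = 29 kcal to 2.80 × 135.4 × √(4/350) = about 41 kcal. If the interaction is tested at the same alpha that sized the trial, the 50/50 figure is 2 × 18 = 36 kcal whatever the SD.

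One interaction contrast has a 5% false-positive rate by design. Six unadjusted contrasts gave at least one false positive in 21% of simulated trials, so a joint test or an adjustment is needed.

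**The case against.** Section 16.1 is a short answer on an ethics form, and the model for comparing strata is often left to a separate statistical analysis plan, which is not at hand. Stratified estimates do not exclude a between-stratum test, and because the strata are independent, a difference and its standard error can be worked out from published stratum estimates. The analyses are also labelled secondary, and the aim uses a weaker verb for subgroups than for the label effects.

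Part of this stands. The protocol does not say that p-values will be compared across strata, so a reader who infers that the plan will generate false subgroup claims goes further than the text. Step 4 shows how far the risk depends on the true effect: 18 kcal is close to the worst case, and reading estimates with intervals would lower the risk. Nor can one infer that no interaction test will ever be run; a separate plan could add one.

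The rest does not remove the point. This is not a detail on which the protocol is silent: it names a method for the subgroup question, and that method does not produce the quantity the aim asks about. The Bonferroni-Holm correction does not help either. At alpha 0.05/6 the discordance rate is still 38% to 46%, and adjusting within-stratum tests does not turn them into a test of a difference.

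**Conclusion.** The point holds as a mismatch between aim and method: differences between subgroups are part of the aim, and the only stated subgroup analysis neither estimates nor tests them. It should be corrected, but it concerns secondary analyses and leaves the primary comparison and the sample size untouched.

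The discordance figures hold only if strata are read by significance and the true effect is near 18 kcal. The uneven splits and all kcal figures rest on assumed stratum shares and a back-solved SD.

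A reader might also take 36 kcal as the trial's smallest detectable difference in effect. At the assumed SD of 120 kcal it is the best case (two equal strata, one unadjusted contrast), and it does not describe a joint test. Unequal strata or adjustment push it up to about 45 kcal; an SD at the low end of the range would lower the unadjusted figure to about 29 kcal.

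**What to change.** In section 16.1, replace the stratification sentence with the following plan.

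- For each named subgroup variable, add condition-by-subgroup interaction terms to the full-sample linear and logistic models.
- Report a joint interaction test per variable, or Holm-adjusted interaction contrasts, and the interaction estimates with 95% confidence intervals.
- Show stratum-specific effects with confidence intervals as description only, and do not infer a difference from significance in one stratum and its absence in another.
- Label these analyses exploratory. Give the detectable difference in effect with its assumptions: for one unadjusted contrast at an SD of about 120 kcal (back-solved range about 97 to 135), at least about 36 kcal with two equal strata, about 39 kcal at 30/70, and about 45 kcal at 20/80 or at 50/50 with alpha 0.05/6. Replace the assumed SD with the one behind section 16.2.

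The cost is a few extra model terms and some wording; no further data or participants are needed. The interaction tests will have low power, 20% to 29% for an 18-kcal difference in effect at the assumed SD. The change therefore guards against misreading more than it promises to detect modest differences.
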